### Surgical methods

Both types of skin closure–transcutaneous stapling and intracutaneous suture–are considered safe and standardized techniques in abdominal surgery. The main surgical procedures are not influenced by the trial protocol. After surgery and closure of the abdominal wall and subcutaneous tissue, merely the type of skin closure will be determined through randomization. The trial is designed for process innovation within standardized therapeutic surgical procedures in an elective setting. No new surgical technique is applied.

### Definition of endpoints and outcome measures

#### Primary endpoint

The primary endpoint is the incidence rate of superficial surgical site infections. Superficial surgical site infection is defined as a category A1 infection according to the CDC, as infection of the incision within 30 days after surgery, involving skin and subcutaneous tissue only and meeting one of the following criteria/clinical signs: (I) purulent secretion, cultural proof of bacteria derived from the tissue covering the incision or any secretion from the incision; (II) pain or tenderness, swelling, redness, warmth; (III) opening of the wound by the treating surgeon; and (IV) diagnosis made by the treating medical doctor.

Type A2 infections are defined as infections within 30 days after surgery and most probably linked to the previous surgical procedure, involving fascia and muscle, and meeting one of the following criteria: (I) purulent secretion from the depth of the incision but not from the organ or visceral cavity; (II) spontaneously opened or opened by a surgeon in case of at least one of the following symptoms: fever (>38°C), localized pain, or localized tenderness; (III) abscess or other signs of infection involving deep tissue layers during another surgery revealed by histopathology or radiology; and (IV) diagnosis made by the treating medical doctor.

Type A3 infections imply infections within 30 days after surgery and most probably linked to the previous surgical procedure and involving the visceral cavity addressed within the previous surgery and meeting one of the following criteria: (I) purulent secretion from a drain addressing the organ or cavity on which the previous surgery was performed; (II) cultural proof of bacteria of a septic secret, organ or cavity; (III) abscess or other signs of infection of the organ or visceral cavity within the clinical examination, subsequent surgery, histopathology, or radiology; and (IV) diagnosis made by the treating medical doctor.

Depending on fulfillment of these criteria, the surgical site infection is assigned to one of the three different categories A1–3, or in case of no infection, “none”. The wound is photodocumented by an independent wound manager on days 2, 5, 10, and 30 after surgery. In case of documented A1–3 infections, the subsequent treatment or procedure is additionally recorded. Category A2 or A3 infections which emerge from deeper layer or even the abdominal cavity and which are not linked to an infection of the upper layer of the skin are not attributed to the method of skin closure and thus do not attribute as failures to the statistical analysis of the primary endpoint.

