[7,8]. Results of randomized controlled trials assessing the impact of different closure techniques on superficial surgical site infections are conflicting in dependence of body region and surgical procedure. Differences in the bacterial spectrum and number of bacteria are likely to be influential. In orthopedic surgery, a meta-analysis comparing the outcome of sutures versus staples on superficial surgical site infections demonstrated superiority of sutures for knee and hip surgery. However, the authors outlined substantial methodological limitations of the primary data and the need for definite randomized controlled trials
[9]. In heart surgery, a systematic review of randomized controlled trials for closure of leg wounds after vein graft harvesting for coronary artery bypass surgery revealed no difference between sutures and staples
[10]. In obstetrics, a recent systematic review and meta-analysis demonstrated the superiority of subcuticular sutures compared to staples for skin closure after caesarean sections; there was no significant difference in the cosmetic outcome
[11].

Regarding abdominal surgery, five randomized controlled trials dating from 1981 to 1992, assessed the outcome of staples versus sutures for skin closure on superficial surgical site infection, pain, operation time, and cosmetic outcome. Three of the trials compared interrupted mattress sutures to staples
[12-14], and two compared intracutaneous sutures versus staples
[15,16], including a comparison of different suture materials
[16]. While in the Pickford trial
[14] the infection rate was significantly lower in favor of staples (6.3% vs. 17%), no significant difference could be demonstrated in the trials of Eldrup
[12] and Gatt
[13]. The two trials comparing intracutaneous sutures to staples showed no significant difference regarding the incidence of superficial surgical site infection. Moreover, the suture material was proven to be of no impact
[16]. All trials, which additionally considered the cosmetic outcome
[13,15,16] and closure time, revealed no significant difference for the cosmetic outcome but a significant reduction of the closure time. However, data addressing postoperative pain were conflicting. Two trials demonstrated a significant reduction of postoperative pain in favor of staples
[12,15], whilst one trial showed no difference

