### Randomization, allocation concealment, and blinding

A random sequence will be generated through computerized random assignment and concealed allocation. Intraoperative randomization will be performed. After closure of the fascia, the anesthetist or the second scrub nurse calls the randomization office to give the patient’s number, surgeon’s name, and ask for allocation. Using the loudspeaker, the surgeon then is de-blinded. The outcome assessment cannot be blinded due to the nature of the study. Therefore, the detection bias is high and cannot be minimized. Skin staples will be visible for the outcome assessors during the follow-up visits from days 1 to 10.

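### As printed, local signs alone or wound opening alone can satisfy the A1 definition, so the primary endpoint can count non-infected wounds, possibly unequally by arm under unblinded assessment

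*Protocol article*

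**What the plan says.** Under Primary endpoint, the protocol article defines A1 "as infection of the incision within 30 days after surgery", "involving skin and subcutaneous tissue only and meeting one of the following criteria/clinical signs". Four criteria follow. The first is pus or a positive culture, and the fourth is a diagnosis by the treating doctor. The second and third read "II) pain or tenderness, swelling, redness, warmth; (III) opening of the wound by the treating surgeon".

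For A2, the corresponding item requires that the wound be "spontaneously opened or opened by a surgeon in case of at least one of the following symptoms", and then names fever, localized pain and localized tenderness.

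The list decides the category: "Depending on fulfillment of these criteria, the surgical site infection is assigned to one of the three different categories". A patient without infection is classed as none. Under Statistical analysis, the primary χ² test compares the proportions of patients with A1 within 30 days.

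On assessment, the section on randomization and blinding says: "The outcome assessment cannot be blinded due to the nature of the study. Therefore, the detection bias is high and cannot be minimized". It adds: "Skin staples will be visible for the outcome assessors during the follow-up visits from days 1 to 10".

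**The concern.** Under a one-of rule, separately numbered items each suffice. Opening of the wound by the surgeon then qualifies with no sign and no stated reason. Local signs qualify without opening, pus or culture, and it is unclear whether one sign is enough or all are needed. Signs of this kind can occur at a fresh laparotomy wound without infection.

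Two things are at stake. If non-infected wounds are added equally to both arms, the contrast shrinks and power falls. If they are added unequally, the test can reject when infection rates are the same, or miss a real difference. Criteria that depend on judgement are where unblinded assessment acts most, and this is the only primary endpoint.

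**Working it through.** **1. The two definitions side by side**

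| | A1 (superficial) | A2 (deep) |
|---|---|---|
| Rule | any one of four criteria | any one of four criteria |
| Opening by surgeon | sufficient alone, no condition | only with at least one of fever, localized pain, localized tenderness |
| Local signs | separate item, sufficient without opening | only as a condition attached to opening |
| Number of signs | not stated | at least one |
| Doctor's diagnosis | sufficient alone | sufficient alone |

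The A1 rule is looser than its deep-infection counterpart, and no reason is given.

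**2. The plan's own figure**

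Inputs from Sample size: 14% (staples), 4% (suture), two-sided 5% χ² test, 80% power, 10% drop-out.

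With mean rate 0.09 and the pooled-variance formula without continuity correction:

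n = [1.960·√(2·0.09·0.91) + 0.842·√(0.14·0.86 + 0.04·0.96)]² / 0.10² = (0.793 + 0.335)² / 0.01 = 127.4, so 128 per group.

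256 / 0.90 = 284.4, so 285 in total. Both figures reproduce. Power at 128 per group is 80.2% by normal approximation and 82.6% by exact enumeration of the χ² test. The sample-size arithmetic is not in question.

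**3. Equal non-specific positives in both arms**

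Let f be the share of uninfected patients counted as A1 through signs or opening alone. The documents give no value, so f is assumed. Observed rate = p + (1 − p)·f. For example, with f = 5%: 0.14 + 0.86·0.05 = 18.3% and 0.04 + 0.96·0.05 = 8.8%.

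| f, both arms | Staples | Suture | Difference | Exact power, 128 per arm | n per arm for 80% (formula in step 2) |
|---|---|---|---|---|---|
| 0 | 14.0% | 4.0% | 10.0 points | 82.6% | 128 |
| 2% | 15.7% | 5.9% | 9.8 points | 73.2% | 157 |
| 5% | 18.3% | 8.8% | 9.5 points | 60.7% | 203 |
| 10% | 22.6% | 13.6% | 9.0 points | 46.4% | 287 |

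The difference barely shrinks. Most of the power is lost because the variance grows with the higher rates.

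**4. Unequal non-specific positives, no true effect**

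The common true rate is 9% (the mean of 4% and 14%), with 128 per arm and exact χ² rejection probability:

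| f, one arm vs the other | Observed rates | Rejection |
|---|---|---|
| 0 vs 0 | 9.0% vs 9.0% | 5.0% |
| 2% vs 5% | 10.8% vs 13.6% | 10.0% |
| 5% vs 10% | 13.6% vs 18.1% | 16.6% |

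Which arm carries the higher f is left open, because the documents do not say.

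**The case against.** The strongest reply is that the stem already requires an infection of the incision, that A1 is tied to the CDC category, and that uninfected wounds are classed as none. On that reading, a wound opened for a seroma or haematoma is not A1. This stands in part: the documents do not show that non-infected wounds will be counted, only that they can be. The stem does not close the gap, however, because the four criteria are the only test of infection offered. If the assessor must first judge infection separately, the list does no work and the endpoint rests on unspecified judgement.

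A reader might also infer stronger claims, which the documents do not support:

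- **That pain alone qualifies.** This is one reading of a comma list that does not say whether one sign or all are needed.
- **That the planned rates prove the rule unworkable.** The 4% and 14% are the clinic's own retrospective A1 rates. If they were collected under this list, they already contain the soft events and step 3 counts them twice. If they look too low for a rule that pain alone satisfies, that may only mean A1 was not applied that way.
- **That miscounting does differ by closure method.** The Background reports that "Two trials demonstrated a significant reduction of postoperative pain in favor of staples", but it calls the pain data conflicting and cites a third trial with no difference. Of the two trials, one used interrupted mattress sutures and only one used the intracutaneous closure tested here. The documents do not say that stapled wounds are easier to open. What supports a differential risk is the unblinded assessment, which the article itself concedes.

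An article may abbreviate an outside classification, and the full protocol may spell out how the criteria combine. But this article sets out the list in full, so the problem is a rule that is stated badly and not a detail left out.

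**Conclusion.** The concern holds as a defect in the stated rule. A1 separates signs from opening where A2 joins them, leaves the number of signs open, and offers no other test of infection. The primary endpoint can therefore include non-infected wounds. With unblinded assessors and visible staples, their share may differ by arm, in a direction and at a rate that the documents do not give.

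The size is illustrative. The power loss in step 3 applies only if the planned rates exclude such events. The excess rejection in step 4 applies only if the shares differ by arm. Neither table is an estimate for this trial.

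**What to change.** - **Definition.** Reconcile A1 with the A2 opening criterion and with the CDC definition that the article invokes, so that local signs and deliberate opening by the surgeon count together and not each alone. State how many signs are needed. Keep pus or a positive culture sufficient alone.
- **Culture result.** Do not add an exclusion for culture-negative openings unless the sponsor confirms it against the CDC text; these documents give no basis for one.
- **Recording.** Capture each component separately, and flag events that rest on the doctor's diagnosis alone. That criterion is also soft, and joining signs with opening leaves it in place.
- **Sensitivity analysis.** Report the primary comparison without events that rest only on signs, opening or the doctor's diagnosis.
- **Patients already enrolled.** Trial status gives an enrolment start of 4 March 2013. Apply the rule to earlier patients where the components were recorded, and fix it before any comparison by arm.

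**Cost.** The change needs revised endpoint wording, case report form fields and a derivation rule. Fewer soft events will be counted. The primary endpoint wording changes during enrolment in an unblinded trial, so the change must be documented as an amendment. Where components were not recorded, some earlier patients cannot be reclassified.

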#### Secondary endpoints

Secondary endpoints comprise time of skin closure, satisfaction of the cosmetic outcome 30 days after surgery, prolongation of hospital stay, and inability to work due to surgical site infections. After randomization and closure of the subcutaneous tissue, the time of skin closure is recorded. Within the follow-up visits, the satisfaction of the cosmetic outcome 30 days after surgery is assessed separately by the patient and an independent wound manager on a scale as used within the German school grade system (1?=?best to 6?=?worst). Moreover, the prolongation of hospital stay and employees’ illness due to surgical site infections are recorded.

### Randomization, allocation concealment, and blinding

A random sequence will be generated through computerized random assignment and concealed allocation. Intraoperative randomization will be performed. After closure of the fascia, the anesthetist or the second scrub nurse calls the randomization office to give the patient’s number, surgeon’s name, and ask for allocation. Using the loudspeaker, the surgeon then is de-blinded. The outcome assessment cannot be blinded due to the nature of the study. Therefore, the detection bias is high and cannot be minimized. Skin staples will be visible for the outcome assessors during the follow-up visits from days 1 to 10.

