### Sample size

The trial is designed on the basis of a critical appraisal of current evidence. Literature data concerning the evaluation of intracutaneous suture and skin stapling with regard to superficial surgical site infections are insufficient. Retrospective data of the own clinic served as reference for calculating the sample size. The standard procedure for skin closure has changed during the past years, i.e., in 2011, the patients routinely received intracutaneous suture, while in 2009, the patients had routinely received skin stapling. Retrospective analysis of these data showed a lower rate of A1 infections for intracutaneous (4%) than for stapling (14%) closure. To achieve a power of 80%, 128 patients per group are needed to detect this difference when applying a two-sided χ^2^ test with a significance level of 5%. Incorporating a rate of drop-outs of 10%, a total of 285 patients need to be randomized.

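### Detection bias is declared beyond reduction, although the treating doctor's diagnosis alone can make a primary event and no planned sensitivity analysis addresses ascertainment

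*Protocol article*

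**What the plan says.** Under Randomization, allocation concealment, and blinding, the protocol article states that the outcome assessment cannot be blinded and continues: "Therefore, the detection bias is high and cannot be minimized". It adds: "Skin staples will be visible for the outcome assessors during the follow-up visits from days 1 to 10". The surgeon learns the allocation over a loudspeaker in theatre.

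Under Primary endpoint, an A1 infection within 30 days needs only one of four criteria: (I) purulent secretion or a positive culture, (II) local clinical signs, (III) opening of the wound by the treating surgeon, or (IV) "diagnosis made by the treating medical doctor". Each patient is then assigned to A1, A2, A3 or no infection. The same section says: "The wound is photodocumented by an independent wound manager on days 2, 5, 10, and 30 after surgery".

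Under Statistical analysis, the primary test is a two-sided chi-square test in the intention-to-treat population. Two kinds of sensitivity analysis are named: the same test in the per-protocol population, and logistic regression adjusted for prognostic factors.

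**The concern.** The protocol names a high bias in its primary endpoint and then says nothing can be done about it. That is a stated position, not a detail left to another document.

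The endpoint is exposed to this bias. Criterion IV is a judgement by a clinician who is not blinded, and it is sufficient on its own. Criteria II and III also depend on the clinician. Changing the analysis population or adding covariates leaves the A1 label as it was, so neither sensitivity analysis can show how far a result depends on who called the infection.

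The stated hypothesis is that suture is better. If assessors call doubtful staple wounds infected more readily than doubtful sutured wounds, the chi-square test would count that as a treatment effect.

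**Working it through.** **Inputs from the documents (Sample size).** Two-sided chi-square test at 5%; A1 rates of 14% with staples and 4% with suture, from the department's retrospective data; "To achieve a power of 80%, 128 patients per group are needed to detect this difference"; 10% drop-out; 285 randomized.

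**Inputs assumed.** The documents give neither an over-calling rate nor the share of A1 events that meet criterion I. Both are shown over a range.

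**Step 1. The plan's own figure.** With pooled variance under the null and no continuity correction, the mean rate is 0.09 and

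n = [1.960·√(2·0.09·0.91) + 0.842·√(0.14·0.86 + 0.04·0.96)]² / 0.10² = (0.793 + 0.335)² / 0.01 ≈ 127.4, so 128 per group.

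The total is 256/0.9 = 284.4, so 285. The sample size reproduces, and this point concerns no arithmetic error.

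**Step 2. What the planned analyses can detect.**

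| Analysis | What changes | Outcome used |
|---|---|---|
| Primary chi-square | – | A1 as assigned |
| Per-protocol chi-square | population | A1 as assigned |
| Adjusted logistic regression | covariates | A1 as assigned |

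None varies how the event is ascertained.

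**Step 3. Effect of over-calling when closure makes no difference.** Let the true rate be p in both arms and let d be added to the staple arm by over-calling. The rejection probability is the sum, over all event counts x (staples) and y (suture), of Bin(x; 128, p + d)·Bin(y; 128, p), taken where |x − y|/128 exceeds 1.960·√(2·m(1 − m)/128), with m = (x + y)/256.

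| Over-calling d | Patients (128·d) | p = 4% | p = 9% |
|---|---|---|---|
| 0 | 0 | 4.5% | 5.0% |
| 2 points | 2.6 | 10.7% | 8.3% |
| 3 points | 3.8 | 17.6% | 12.2% |
| 5 points | 6.4 | 36.5% | 23.8% |

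At 5 points practically all rejections favour suture. If d is instead read as the percentage of uninfected staple wounds called A1, the figures for 5% are 34.4% and 20.8%, which leads to the same conclusion.

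**Step 4. What a restricted endpoint can show.** Suppose a share f of A1 events meets criterion I, equally in both arms. The rates are then 0.14f and 0.04f. With m = 0.09f, power at 128 per arm is Φ{[0.10f·√128 − 1.960·√(2m(1 − m))] / √[0.14f(1 − 0.14f) + 0.04f(1 − 0.04f)]}.

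| f | Rates | Power |
|---|---|---|
| 1.0 | 14% vs 4% | 80% |
| 0.8 | 11.2% vs 3.2% | 70% |
| 0.6 | 8.4% vs 2.4% | 57% |
| 0.5 | 7.0% vs 2.0% | 49% |
| 0.4 | 5.6% vs 1.6% | 40% |

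A non-significant restricted result would therefore not prove an assessor effect.

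**Step 5. Would agreement in direction work as a gate?** A simulation used 5 points of over-calling, all outside criterion I, with 50–100% of true events meeting criterion I. Superiority was claimed only if the criterion-I count was also higher with staples. The false-positive rate in favour of suture falls only from 37% to 24–30% (p = 4%) and from 24% to 19–23% (p = 9%). Significant results tend to arise when chance already favours suture, so the directions usually agree.

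**The case against.** The article discloses the limitation openly, uses published CDC criteria and provides independent photographs. Supplementary analyses and case report fields are often left to the full protocol or analysis plan. This would be decisive if the point were only that an analysis is missing. It does not cover a positive statement that the bias cannot be reduced.

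The over-calling rates are assumptions, and all the bias is taken to run against staples. Five points on a 4% base more than doubles the event rate, and at a 9% base 2–3 points give only 8–12%. This stands. The figures show vulnerability and do not predict what will happen.

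Criterion I is not free of bias. No scheduled culture is described, so staff who know the allocation may decide when to sample. This also stands.

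A reader might go further in four ways that the documents do not support:

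- **That criterion-level data are already collected.** The article describes assignment to a category according to the criteria, but does not say that the criterion met is recorded.
- **That the department moved to suture because of its own infection data.** Sample size says only that routine closure differed between 2009 and 2011. The retrospective comparison was made to prepare the sample size, and data from patients already being sutured cannot have prompted the change to suture.
- **That the wound manager or the day-30 visit offers ready masking.** The wound manager is called independent, not masked. Three of the four photographs fall within the days when staples are visible. If the same person attends throughout, withholding the operation note at day 30 masks nothing, and real masking would need another assessor.
- **That a significant result could not be read as an effect of closure at all.** The calculation does not support so flat a statement.

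**Conclusion.** The point holds in a limited form. The claim that detection bias cannot be reduced does not follow from the inability to blind bedside assessment. The primary endpoint can rest on an unblinded opinion alone, and neither planned sensitivity analysis addresses ascertainment.

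Under assumed over-calling of 2–5 points in the staple arm, with no true difference and 128 per arm, the rejection rate rises from about 5% to 11–37% at a 4% true rate, or to 8–24% at a 9% true rate. These figures depend on the assumed rates and on the bias running against staples only.

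Restricting the endpoint to criterion I lessens the bias without removing it, and leaves power of roughly 40–70% if 40–80% of events qualify. It can therefore inform the size and direction of the effect. It cannot serve as a test on which superiority depends.

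**What to change.** 1. In the blinding section, state that detection bias cannot be eliminated, in place of the claim that it cannot be minimized.
2. Record for each event which of criteria I–IV was met.
3. Pre-specify two supportive analyses of the primary endpoint: one restricted to criterion I (purulent secretion or positive culture), and one excluding events that rest only on criterion IV. Report each as an estimate with a 95% confidence interval, and use them to judge the size and direction of the effect. Do not make them a condition for claiming superiority.

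The cost is one field in the electronic case report form, two further tables and a few sentences. The primary analysis and sample size do not change. The drawback is fewer events and wider intervals, and the report should say that criterion I remains partly exposed because no scheduled culture is described.
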